#### Bin and contents inspection

Each RUM bin will be visually inspected prior to opening to record the source of the bin (state/territory and wholesaler returning the bin), container weight and bin identification number. On opening the bin, the contents are spread over a table and visually inspected for any signs of hazardous materials. If inappropriate items are found, the bin is to be immediately resealed and sent for incineration. RUM bins will be excluded from further assessment if they: are less than 50% full; or contain a high proportion of general waste; or contain more than 50% loose tablets (not in an identifiable bottle/packet or blister/strip); or contain hazardous items such as broken glass, biological waste, unknown liquid or powder waste.

Once it is decided that a bin is suitable for auditing, details of each discarded medicine will be recorded in the database. Information recorded includes the name of the medicine (brand or generic), strength and pack size. The expiry date, schedule, if there is a dispensing label present, dispensing category and year dispensed is then recorded, together with the quantity returned. For items that are a unit dose (i.e. tablets, capsules, nebules, prefilled syringes, etc.), the exact number of units returned is counted. For liquids, the percentage returned is estimated (empty = 0%; 1–25% = 25%; 25–50% = 50%; 50–75% = 75%; and 75–100% = 100%) and creams, gels and ointments are weighed to assess volume remaining. The amount remaining in aerosols is recorded from the dose indicator or estimated by placing the device/canister in water to determine whether it is full (quickly sinks), used (slowly sinks) or empty (floats). Loose tablets and capsules (i.e. those not in bottles or blister packs) and products that are unidentifiable (e.g. from another country or not in original packaging) will be excluded. Volumes of complementary and/or alternative medicines returned will be estimated rather than counted (0–25%, 26–50%, 51–75% or 76–100% full).

If dose administration aids are present, the type (e.g. dosette, blister or sachet pack) is to be recorded and proportion remaining estimated (e.g. 0%–25%, 26%–50%, 51%–75%, and 76%–100% full).

When an item is identified as a Schedule 8 (controlled) medicine, this will be recorded specifically in the database, together with any evidence of destruction (i.e. cut and empty foil strip or an empty bottle).

If any sharps are present, including any used or unused needles and syringes, lancets, and blades [23, 24], this will also be recorded specifically in the database.

A number of quality assurance processes have been built into the audit to ensure safety and adherence to legislation, audit protocols and data entry processes. For example, re-inspection and checking of data entered for the first RUM bin and a second, randomly selected bin for each pair of data collectors.

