#### Sample size and RUM bin selection

The design of the audit must ensure that a statistically relevant sample of RUM bins from all Australian states and territories are included (*n* = 8). Over the last three years (2013–2015), data provided by NatRUM Ltd. showed that an average of 10–12,000 bins per month were collected for incineration. For the purposes of calculating the minimum sample size for a statistically valid sample of RUM bins in this study, 12,000 bins per month was used in the Raosoft® sample size calculator (http://www.raosoft.com/samplesize.html); a minimum of 373 bins would need to be sampled (assuming 5% margin of error and 95% confidence interval).

Table 1 outlines the number of RUM bins calculated to ensure an Australian-wide representative sample of 373 bins. Based on the 2013 audit [20], it was estimated that an additional 10% (37 bins) would require inspection to ensure that no bins contained more than 50% as loose tablets/capsules i.e. without any form of packaging (see exclusion criteria listed in *Bin contents and inspection* section).

**Table 1 Tab1:** Selection of RUM bins required for audit^a^

State/territory	Average number of pallet collections per month	Average number of bin collections per month	Percentage of bins (%)	Number of bins to be audited
Australian Capital Territory	2	96	0.8	3
New South Wales	79	3792	30.4	113
Northern Territory	2	96	0.8	3
Queensland	48	2304	18.5	69
South Australia	37	1776	14.2	53
Tasmania	4	192	1.5	6
Victoria	68	3264	26.2	97
Western Australia (including Christmas Island)	20	960	7.7	29
TOTAL	260	12,480	100	373

^a^
*Pellet Collections by region (first six months of 2015/2016): National data (excluding Western Australia) provided by NatRUM Limited. Data for Western Australia provided by the Western Australia Incineration Site*

Incineration contractors at the three licensed plants (located in Victoria, Queensland and Western Australia) will be requested to randomly select and set aside one bin in every ten from each sequential pallet arriving from all states or territories in the month prior to the audit, until the total (plus 10%) for that site is achieved.

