#### Data collection and training

Data collection tools and protocols developed specifically for the 2013 NatRUM audit were reviewed and refined to ensure that the audit will build on, and extend, the evidence base; e.g. whether medicines have been used (opened or full pack) and calculating the proportion of medicine that is returned (compared with 2013 where all medicine packs were treated as unopened and 100% contents were assumed) [20]. Additional variables were identified from a similar audit in New Zealand (DUMP project [22]) and in consultation with the NatRUM Ltd. Board. Table 2 outlines the variables, to be included in the audit. A purpose-built database has been developed in Microsoft Access®. We used Australian Medicines Terminology (AMT) - a subset of the SNOMED CT-AU clinical terminology, supported by the Australian Digital Health Agency (http://www.digitalhealth.gov.au/get-started-with-digital-health/what-is-digital-health/clinical-terminology remove extra line here and rejoin sentence). This national terminology unambiguously identifies branded and generic medicines commonly used in Australia. It includes a list of most prescription and OTC medicines and complementary products sold in Australian pharmacies, allowing generic and/or trade names to be easily searched and data such as form, strength and original quantity to be easily selected. For items not available in this list, manual entry of the name of the product, form, strength and original pack quantity will be required. The database and data collection process have been piloted with three RUM bins at the Queensland incineration plant and a number of modifications were implemented. The Access® database has been loaded onto laptop computers for data entry in real time at each incineration site.

**Table 2 Tab2:** Variables to be included in RUM audit and post-audit analyses

Characteristics of RUM bins	Source of container (state or territory)
	Container weight
	Percentage filled
Content of RUM bins	Medicine characteristics
	Brand name
	Generic name
	Manufacturer
	Medicine schedule (i.e. unscheduled, S2, S3, S4 or S8)
	Therapeutic category (PBS code)
	Medicine dose
	Form of medicine
	Whether medicine is PBS subsidised or private
	Whether medicine is expired
	Packaging of medicine included
	Evidence of attempted destruction for S8 medicines
	Presence of inappropriate items (e.g. sharps, rubbish)
	Complementary and alternative medicines
	Medicine in a sample package

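### The reseal rule removes bins holding inappropriate items, yet inappropriate items and sharps are audit variables; read literally, their recorded prevalence is biased downward by an unknown amount

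*Protocol article*

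**What the plan says.** All the relevant text is in Stage one of the protocol article.

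- **First look** (Bin and contents inspection). Source, weight and identification number are recorded before opening. Then: "On opening the bin, the contents are spread over a table and visually inspected for any signs of hazardous materials".
- **Reseal rule** (next sentence). "If inappropriate items are found, the bin is to be immediately resealed and sent for incineration". It gives no threshold and mentions no entry in the database.
- **Exclusion list** (the sentence after that). Among other grounds, bins are excluded if they "contain a high proportion of general waste" or "contain hazardous items such as broken glass, biological waste, unknown liquid or powder waste". Sharps are not named.
- **Item-level recording** (same section). "Once it is decided that a bin is suitable for auditing, details of each discarded medicine will be recorded in the database".
- **Sharps** (end of the same section). "If any sharps are present, including any used or unused needles and syringes, lancets, and blades", this is to be entered specifically in the database.
- **Table 2** (Data collection and training). One of the bin-content variables is "Presence of inappropriate items (e.g. sharps, rubbish".
- **Reserve** (Sample size and RUM bin selection). Beyond the 373 bins, "it was estimated that an additional 10% (37 bins) would require inspection". The reason given is bins with more than half their contents as loose tablets or capsules.

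**The concern.** Table 2 and the reseal rule use the same term. The only examples the protocol gives for it, sharps and rubbish, therefore name things that both remove a bin from the audit and are to be measured in the audit. The exclusion list adds a second conflict: a threshold for general waste has no function if any rubbish already causes resealing.

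At stake is the audit's evidence on what goes into the bins that should not. If the bins with these items drop out without an entry, the figure reported from the remaining bins understates the problem. The loss cannot be repaired afterwards, because the resealed bins are incinerated. The quality check given as an example (re-inspecting two bins per pair of collectors) would not bring back bins that were never entered.

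**Working it through.** **1. The rules side by side**

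| Bin contains | Reseal rule | Exclusion list | Recording rules |
|---|---|---|---|
| Any sharps | Remove, if the Table 2 examples define the term | Not named | Record |
| A little rubbish | Remove, on the same reading | Keep | Record |
| Much general waste | Remove | Remove | Record |
| Broken glass, biological waste | Remove | Remove | Not named in Table 2 or the sharps sentence |

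The first two rows contradict each other. In the third row both removal rules agree, but Table 2 still wants the item recorded and no step says when.

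**2. Direction and size of the bias**

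Let π be the true share of bins with inappropriate items, and s the share of those bins that leave without a record. Assume that the other exclusions are unrelated to these items. Prevalence among audited bins is then

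π(1 − s) / (1 − πs).

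This is below π whenever s > 0 and π < 1, because then 1 − s < 1 − πs. The direction is therefore fixed; the size depends on two quantities that the documents do not give. With assumed values:

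| True π | s = 0 | s = 0.5 | s = 0.9 | s = 1 |
|---|---|---|---|---|
| 5% | 5% | 2.6% | 0.5% | 0% |
| 10% | 10% | 5.3% | 1.1% | 0% |
| 20% | 20% | 11.1% | 2.4% | 0% |
| 30% | 30% | 17.6% | 4.1% | 0% |

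Example: 0.10 × 0.1 / (1 − 0.10 × 0.9) = 0.01 / 0.91 = 1.1%.

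On the literal reading, s is the chance that the first look finds the item. On the narrower reading (only hazardous items or much general waste remove a bin), s is smaller but not zero, and the bins lost include those with the most rubbish. If presence is entered at opening and all opened bins are the denominator, this mechanism causes no bias.

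**3. Sample size**

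The plan's figure reproduces. With N = 12,000, e = 0.05, 95% confidence and p = 0.5 (assumed, not stated), x = z²p(1 − p) and

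n = Nx / ((N − 1)e² + x) = 372.26, rounded up to 373.

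The reserve is 0.10 × 373 = 37.3, stated as 37, so 410 bins are set aside. They yield 373 only if exclusions on all grounds stay at or below 37 / 410 = 9.0%. If resealing alone took an assumed 10% to 30%, 410 − 41 = 369 to 410 − 123 = 287 would remain. The margin of error, 1.96 × √(0.25/n) × √((N − n)/(N − 1)), would be 5.0% at 369 and 5.7% at 287, against the planned 5%.

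**The case against.** The best defence is context. The sentence before the reseal rule speaks of hazardous materials, and the sentence after it lists hazardous items and a large amount of general waste. Read that way, the rule covers hazardous contents only, and bins with sharps or some rubbish stay in and are recorded. This reading is plausible, and it gives the general-waste threshold a purpose. But it is an inference against the protocol's own use of the term in Table 2, and it still loses the bins with the most rubbish unless they are logged first.

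The second defence is that one collector inspects while the other enters data in real time, so an entry before resealing is possible. That is true, and the text does not rule it out. A condensed article may also leave item definitions to the training tools, which are available on request. Missing detail would be no finding; conflicting printed rules are one.

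Four stronger readings are tempting and are not supported:

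- *Recorded prevalence will be near zero.* This needs the broad reading, high detection at first look and no entry for resealed bins. The text settles none of these.
- *The bins are never opened.* They are opened, spread out and inspected before any resealing.
- *Plants will show false differences.* About 15 pairs work at three sites, and the Limitations section itself names standardisation as a challenge, but no comparison between plants is planned.
- *The audit will fall short of 373.* No reseal rate is given, so this cannot be asserted.

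It also stands that inappropriate items are not part of a stated Stage One objective. Those concern the amount and types of medicines returned, and the PBS-subsidised share and its value.

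**Conclusion.** The contradiction is in the printed text and should be resolved before bins are opened. As written, the prevalence of inappropriate items and sharps has no defined numerator or denominator. On the literal reading it is biased downward by an amount that the documents do not allow one to compute; the figures under working show only how the bias would behave under assumed rates. On the narrower reading the bias is smaller, but does not vanish unless excluded bins are logged.

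The reserve is a secondary matter. It is sized for one ground of exclusion although several apply, with a tolerance of 9.0% in total. Even the assumed losses of 10% to 30% would widen the margin of error only from 5.0% to 5.7%. The effect is confined to a secondary descriptive variable, but the correction is cheap and the loss would be permanent, so the change should be made.

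**What to change.** 1. Reconcile the reseal rule, the exclusion list, the sharps sentence and Table 2. State which items trigger resealing and which are only recorded. This review takes no position on which safety rule is right, and none needs to change for the audit's purposes.
2. For every opened bin, including those then resealed or excluded on any ground, enter the presence and type of inappropriate item and the reason for exclusion before the bin is closed. Source, weight and identification number are already captured before opening.
3. Report prevalence with all opened bins as the denominator. For resealed bins, note that the types recorded are those visible at first look.
4. State that the reserve has to cover all grounds for exclusion, and report the number excluded on each.

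The cost is one or two bin-level fields in the existing Access database, one paragraph of text, and a short addition to the collectors' training.

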#### Data analysis

For data collection purposes, *trade product pack terms* are used, allowing data collection personnel to search and select on branded or generic names of products, for example:Panadeine Caplet® (codeine phosphate hemihydrate 8 mg + paracetamol 500 mg) tablet: film-coated, 12 tablets.

Use of the AMT allows linkage between trade product pack terms with other formal definitions such as the *medicinal product pack term*:paracetamol 500 mg + codeine phosphate hemihydrate 8 mg tablet, 12 tablets; and *the medicinal product term*:paracetamol + codeine.

Following data collection the trade product pack terms will be matched with both the medicinal product pack and medicinal product terms (using the SNOMED CT-AU v1.7 Common Release). AMT is also compatible with PBS data and hence the PBS dataset will be merged, along with the Anatomical Therapeutic Chemical (ATC) classification system number, into the bin audit database. This allows PBS items to be matched with a price (Manufacturer’s ‘Ex-Manufacturer Price’ for a manufacturer’s pack).

Automated matching will not be possible for manually entered items (where no trade product pack listing was available at data entry), requiring manual matching in some instances. Following data matching, audit data will be cleaned in preparation for visualisation and descriptive data analyses. Using a number of assumptions an extrapolated value of ‘wastage’ to the PBS will be estimated. This estimate is sensitive to the definition of waste, such as whether only unopened packs are counted, whether products were expired at the time of counting (but not necessarily at the time of disposal), and if a dispensing label was visible. Four assumptions will be tested and presented alongside the main results: i) dispensed, unopened, not expired; ii) dispensed, unopened, expired and not expired; iii) dispensed, opened and unopened, and not expired; and iv) dispensed, opened and unopened, expired and not expired.

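### Stage One drops part-full, waste-heavy and mostly loose-tablet bins, putting per-bin extrapolation at risk of overstatement, and its four PBS value scenarios never vary label visibility, a driver the plan names

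*Protocol article*

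**What the plan says.** The Study design overview gives Stage One two aims: to describe how much and what is returned, from a statistically valid sample of bins, and to extrapolate the value of wastage to the PBS.

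The section Bin and contents inspection then filters the sampled bins. "RUM bins will be excluded from further assessment if they: are less than 50% full; or contain a high proportion of general waste". Bins also go if they "contain more than 50% loose tablets (not in an identifiable bottle/packet or blister/strip" or hold hazardous items. Inside audited bins, loose and unidentifiable items are not counted. Container weight is recorded before opening, and Table 2 lists "Percentage filled" as a bin characteristic.

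On numbers, "12,000 bins per month was used in the Raosoft® sample size calculator", giving "a minimum of 373 bins would need to be sampled (assuming 5% margin of error and 95% confidence interval". For losses, "it was estimated that an additional 10% (37 bins) would require inspection to ensure that no bins contained more than 50% as loose tablets/capsules".

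On value, the Stage one Data analysis section says the estimate depends on how waste is defined. It gives three examples: whether only unopened packs count, whether the product has expired, "and if a dispensing label was visible". It continues: "Four assumptions will be tested and presented alongside the main results: i) dispensed, unopened, not expired". Scenarios ii to iv complete the combinations of opened status and expiry, and each also requires a dispensed item. How the audited value is scaled up is not stated. The Limitations section does not mention the bin exclusions.

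**The concern.** A bin under half full is a real bin with a small amount in it. Removing it truncates the sample on the quantity being measured. A waste-heavy bin is likewise part of the scheme's load, with less medicine per kilogram. If the mean of the remaining bins is applied to all bins collected, the excluded ones are credited with contents they may not have. Inspecting extra bins replaces the number lost but not the kind lost.

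The second weakness is separate. The scenarios are there to show how far the PBS value moves with the definition of waste. The plan names label visibility as one reason it moves, and then holds it fixed. A reader would take the spread of the four figures as covering the plan's own list of drivers, which it does not.

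The PBS value is a stated objective, and the Abstract says results will inform the Federal Department of Health.

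**Working it through.** **1. The plan's own figure.** With N = 12,000, margin m = 0.05, z = 1.96 and p = 0.5 (my assumption, as the article gives no proportion), x = z²p(1−p) = 0.9604. Then n = N·x / ((N−1)m² + x) = 11,524.8 / 30.958 = 372.3, so 373. The stated figure is reproduced, the Table 1 allocations add to 373, and this point does not affect that calculation.

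**2. The inspection allowance.** 373 + 37 = 410 bins. All 373 are kept only if exclusions on every criterion together do not exceed 37/410 = 9.0%. The allowance is justified for loose tablets alone. It says nothing about how many bins are under half full or waste-heavy.

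**3. Per-bin scaling and fill.** The article does not give the share e of bins under half full or the fill levels. Assume mean fill 30% in those bins and 85% in the rest. Overstatement = 0.85 / ((1−e)·0.85 + e·0.30) − 1.

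- e = 5%: 0.85/0.8225 − 1 = 3.3%
- e = 10%: 0.85/0.795 − 1 = 6.9%
- e = 20%: 0.85/0.74 − 1 = 14.9%

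A wider set of assumptions gives the same picture. If a share e of bins is excluded for any reason, with value r relative to audited bins, the ratio is 1/((1−e) + e·r). For r between 0.25 and 0.5, the overstatement is 5–8% at e = 10%, 11–18% at 20% and 18–29% at 30%. At r = 1 there is none.

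**4. Per-kilogram scaling.** If value per kilogram is similar in part-full and fuller bins, fill largely cancels. The other exclusions do not. Let excluded bins carry a share w of the weight, with value per kilogram v relative to audited bins; the ratio is 1/((1−w) + w·v). At w = 10%:

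- v = 0.25: 1/0.925 = 1.081, overstated
- v = 0.5: 1/0.95 = 1.053, overstated
- v = 1.5: 1/1.05 = 0.952, understated

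Waste-heavy bins should have v below 1. Loose-tablet bins may have v above 1, because loose tablets carry no cartons or bottles.

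**5. The label.** The scenarios set against the drivers the plan names:

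| Driver | Varied in i–iv? |
|---|---|
| Opened or unopened | Yes |
| Expired or not | Yes |
| Dispensing label visible | No; *dispensed* is required in all four |

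Suppose *dispensed* is judged from a visible label and a share u of dispensed PBS value has none (assumed equal across scenarios). Each scenario then captures 1 − u of that value, and including the rest would multiply it by 1/(1−u): 1.11, 1.25 and 1.43 at u = 10%, 20% and 30%.

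**The case against.** The strongest reply is that no bias has been shown. The article condenses a fuller protocol and does not state the scaling rule. That rule could be by weight, or could adjust for fill, since both are recorded. This stands: the missing rule is not itself an error, and the conclusion must be put as a risk.

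A reader might infer that the PBS value will be too high whichever way it is scaled. The documents do not support that. Weight scaling largely cures the fill problem, and loose-tablet bins could push the result down. Uncounted loose items and any label requirement also pull down. The net direction is unknown.

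A reader might also infer that the main result leaves out all unlabelled packs. That is not established. The article never equates *dispensed* with a visible label, although a label is the sign of dispensing that auditors are told to record. The four scenarios are shown alongside main results whose definition is not given. The drivers are introduced as examples, and restricting to dispensed items is a defensible basis for a cost to the PBS. What remains is that a driver the plan itself names is not varied.

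Finally, the audit was adapted from the 2013 one so that outcomes can be compared. Changed inclusion rules could disturb that, which is a reason to report both ways rather than keep the filter alone. Excluding hazardous bins is a safety matter and is not disputed.

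**Conclusion.** The concern holds as a risk, in two parts. First, the exclusion rule as written selects audited bins on amount, and neither the 10% allowance nor the Limitations section deals with it. A per-bin extrapolation would be overstated by about 3–15% if 5–20% of bins are under half full with mean fill 30% against 85%. Those inputs are assumptions, since the article gives no data on them. Per-kilogram scaling largely removes this, leaves the general-waste problem, and has no known direction for loose-tablet bins.

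Second, the four scenarios cover two of the three drivers the plan names. If *dispensed* means labelled, and 10–30% of dispensed PBS value is unlabelled (again assumed), each scenario would rise by a factor of 1.11 to 1.43 once that value was included.

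The two parts can offset each other, so it cannot be concluded that the reported value will be too high or too low. The 373-bin calculation is correct for its inputs.

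**What to change.** 1. Audit part-full bins that are otherwise suitable. Report results with and without them, so that a version under the 50% rule remains for the 2013 comparison.
2. For every other excluded bin, log weight (already taken before opening), fill and reason, without auditing hazardous contents.
3. State the extrapolation rule. Keep all sampled bins in the denominator and scale by weight to the total incinerated. The Background section gives a yearly total of 705,079 kg for 2015/16; the current total on the same weight basis should be used.
4. Show excluded bins at zero identified value and at the audited-bin mean per kilogram. With 10% of weight excluded, the first figure is 0.90 of the second. Present this as a sensitivity range, not as strict bounds, because loose-tablet bins could exceed the audited mean.
5. Define *dispensed*. Add label scenarios that include unlabelled PBS-listed S4 and S8 items and leave out those recorded as private or sample packs: one for unopened packs, one for opened plus unopened, each with its expiry rule stated.

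The cost is a little more auditing and table work, and possibly a lower mean amount per bin. The label scenarios use variables already in Table 2 (schedule, PBS or private status, sample package, unlabelled), so they need no new data collection.

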	Medicines characteristics once dispensed
	Year dispensed^a^
	Quantity dispensed^a^
	Quantity returned^a^
	Evidence of medicine use^a^
	Proportion of dispensed quantity unused^a, b^
	Medicine unlabelled
	Category of medicine dispensing (e.g. concession or general)^a^
	Dose administration aids (DAA)
	Type of DAA
	Proportion of medicines unused in DAA

*PBS = Pharmaceutical Benefits Scheme; S2 = Pharmacy medicine; S3 = Pharmacist-only-medicine; S4 = Prescription medicine; S8 = Controlled medicine*

^a^
*These variables extend the evidence base of data collected during the 2013 audit*

^b^
*Only medicines packaged as foil strips/blisters will be counted and assumptions used in the New Zealand DUMP project audit* [22] *will be applied to documentation of quantity of returned inhalers, creams, liquids*

Audit training tools, including a data collection protocol and quality assurance procedure, and Occupational Health and Safety (OH&S) Standard Operating Procedure (SOP) were developed in consultation with incineration plant managers, personnel from Griffith University OH&S and NatRUM Ltd. (all training tools and protocols are available from correspondence author on request).

Data collection will be conducted at each of the three incineration sites by research assistants, working in pairs (one person inspects and counts whilst the second enters the information into the database), under the supervision of the project Data Collector Manager, (a registered pharmacist). An additional research assistant will be available at each site to act in a quality control role and to provide cover for breaks and/or absences such as unexpected illness. Data collectors will be trained at each site to safely audit a RUM bin and to enter data into the Access® database. Training will include familiarisation with the specific auditing equipment including protective clothing (gloves, safety glasses, dust masks, coveralls), and tools (tongs, tweezers, scales), and a demonstration of how to safely open and assess the contents of a RUM bin. Training will also emphasise the importance of the confidential nature of bin contents including any pharmacy, prescriber and patient information. A representative from Griffith University OH&S will be present for this training.

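### Part-used liquids are scored at the top of overlapping quarter bands, about 12.5 points of a pack too high on average if fill is uniform; separately, a Table 2 footnote conflicts with the counting rule for unit-dose items

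*Protocol article*

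**What the plan says.** All places are in the protocol article, Stage one.

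- **Liquids** (Bin and contents inspection): "For liquids, the percentage returned is estimated (empty = 0%; 1–25% = 25%; 25–50% = 50%; 50–75% = 75%; and 75–100% = 100" per cent.
- **Complementary and alternative medicines** (same section): "Volumes of complementary and/or alternative medicines returned will be estimated rather than counted (0–25%, 26–50%, 51–75% or 76–100% full". No point score is attached to the bands.
- **Dose administration aids** (same section): "proportion remaining estimated (e.g. 0%–25%, 26%–50%, 51%–75%, and 76%–100% full". Again there is no point score.
- **Unit-dose items** (same section): "For items that are a unit dose (i.e. tablets, capsules, nebules, prefilled syringes, etc.), the exact number of units returned is counted". The exclusion covers only "Loose tablets and capsules (i.e. those not in bottles or blister packs" and unidentifiable products, so identifiable tablets in bottles stay in and fall under the exact count.
- **Footnote b of Table 2** (Data collection and training), attached to the proportion of the dispensed quantity that is unused: "Only medicines packaged as foil strips/blisters will be counted and assumptions used in the New Zealand DUMP project audit" will be applied to inhalers, creams and liquids. Those assumptions are not given.
- **Purpose** (Data collection and training): measuring the proportion returned is presented as an advance on the 2013 audit, which took every pack as unopened with full contents.
- **Valuation** (Data analysis, Stage one): of the four wastage scenarios, i and ii use unopened packs only, and iii and iv include opened packs.

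**The concern.** Assigning each band its maximum gives an error in one direction. A bottle with 5% left is recorded as 25%, and one with 76% left as 100%. For the top band, this brings back the full-contents assumption that the new measurement was meant to replace. Auditing more bins does not reduce the error. The four wastage scenarios vary opened status and expiry but not the liquid score, so they would not reveal it.

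The shared edges leave a bottle at exactly 25, 50 or 75% with two permitted scores. Limitations expects around 15 pairs of data collectors and names standardisation as a challenge.

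The footnote raises a different problem. Bottled tablets, nebules and prefilled syringes are counted under one rule and not under the other. The bins go to incineration, so a quantity left uncounted is unlikely to be recoverable.

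**Working it through.** **Inputs.** The scoring map is from Bin and contents inspection. The article does not give the distribution of true fill. I assume uniform fill as the base case and beta shapes with mean fill from 17% to 83% as the range. The article states no bias figure to reproduce.

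**1. Within a band.** If fill is uniform within a band, overstatement = upper limit − midpoint.

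| Band | Midpoint | Score | Excess, points | Relative excess |
|---|---|---|---|---|
| 0–25 | 12.5 | 25 | 12.5 | 100% |
| 25–50 | 37.5 | 50 | 12.5 | 33% |
| 50–75 | 62.5 | 75 | 12.5 | 20% |
| 75–100 | 87.5 | 100 | 12.5 | 14% |

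If the lowest band starts at 1%, its midpoint is 13 and its excess 12.0 points (92%).

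**2. Over all part-used liquids.** With S(x) the share of items fuller than x%, mean score = 25 × [S(0) + S(25) + S(50) + S(75)].

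- Uniform: 25 × (1 + 0.75 + 0.50 + 0.25) = 62.5, against a true mean of 50. Excess 12.5 points, or 12.5/50 = 25%.
- Beta(1,2), mostly low: 25 × (1 + 0.5625 + 0.25 + 0.0625) = 46.9, against 33.3. Excess 13.5 points (41%).
- Beta(2,1), mostly high: 25 × (1 + 0.9375 + 0.75 + 0.4375) = 78.1, against 66.7. Excess 11.5 points (17%).
- Beta(1,5), mean fill 16.7%: 31.7 recorded, excess 15.1 points.
- Beta(5,1), mean fill 83.3%: 93.3 recorded, excess 9.9 points.

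**3. Single items.** 1% full scores 25 (+24). 24% scores 25 (+1). 99% scores 100 (+1). Exactly 50% scores 50 (0) or 75 (+25), depending on the band chosen, and the same holds at 25% and 75%. The range is 0 to 25 points.

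**4. Diluted by unopened packs.** An unopened pack is correctly scored 100. If a share f of liquids is unopened and full (an assumption), the mean excess over all liquids under uniform fill is 12.5 × (1 − f): 9.4, 6.3 and 3.1 points for f = 25%, 50% and 75%.

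**5. Midpoint scoring.** Midpoints lower every part-used score by 12.5 points, so the error is the excess in step 2 minus 12.5. It is 0 under uniform fill, 15.1 − 12.5 = +2.6 at beta(1,5) and 9.9 − 12.5 = −2.6 at beta(5,1). Applied to unopened packs as well, midpoints would understate each by 12.5 points, so those must stay at 100%.

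**6. Footnote against inspection section.** No arithmetic applies. For the same variable, the footnote counts only foil strips and blisters. The inspection section counts tablets, capsules, nebules and prefilled syringes exactly and excludes only tablets and capsules outside bottles or blisters. Both cannot hold for a bottle of tablets, a nebule or a prefilled syringe.

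**The case against.** Several points on the other side stand.

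- A reader might infer that every part-used liquid is overstated by 12.5 points. It is not: that is an average under assumed uniform fill, and a single item can be exact.
- A reader might infer that the wastage total is inflated by 25% or a similar amount. The article gives neither the share of liquids among returned items nor their PBS value. It also does not say how the recorded fraction enters the valuation, and refers to a price for a manufacturer's pack. That liquid scores reach scenarios iii and iv is a reasonable inference, not stated text.
- Opened status is recorded separately, so part-used bottles scored at 100% do not enter scenarios i and ii.
- The upper-limit bias can be corrected after collection. Each score maps to one band, and opened status separates full packs from part-used ones at 100%.
- Fill is judged by eye and 25% reads naturally as belonging to the lower band, so the shared edges are a lesser defect.
- A reader might infer that footnote b also contradicts the rules for creams ("creams, gels and ointments are weighed to assess volume remaining"), inhalers and liquids. The New Zealand audit's assumptions are not shown and may be the same methods, so the article does not support this.

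Two things remain. The stated scoring rule is biased in one direction. The counting conflict for unit-dose items outside foil or blisters does not depend on any unseen source and could not readily be repaired after incineration.

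**Conclusion.** The point holds in a limited form. Scoring at the upper limit overstates part-used liquids by 12.5 points of a pack on average if fill is uniform, about 10 to 15 points over the other shapes tried, and 0 to 25 points per item. This assumes that collectors choose the correct band. The bias affects the proportion unused and, if the recorded fraction is used in the valuation, scenarios iii and iv. Its effect on total PBS wastage is unknown. The shared band edges are a smaller, avoidable source of inconsistency, since the same section uses separate limits for two other product groups. The conflict between footnote b and the exact count is a plain contradiction for bottled tablets, nebules and prefilled syringes, and rests on no distributional assumption.

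**What to change.** 1. Give liquids non-overlapping bands, as the section already does for complementary medicines and dose administration aids, and keep the band code in the database.
2. Analyse opened liquids at 12.5, 37.5, 62.5 and 87.5%. Keep empty at 0% and unopened packs, identified from the Table 2 variable on evidence of use, at 100%.
3. Report lower-limit (0, 25, 50, 75%) and upper-limit scoring of opened liquids as bounds, beside scenarios iii and iv if the fraction enters them.
4. Reconcile footnote b with Bin and contents inspection so that one counting rule covers unit-dose items in every kind of packaging, before the selected bins are incinerated.

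The cost is a small change to the data-entry bands in a database already piloted and loaded onto laptops, one footnote edit and a short rescoring step. The stated wastage figure will be lower wherever the liquid fraction enters it. Item 2 could still be done after collection; items 1 and 4 need to be settled before it.
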